#### Pain intensity

An overall between-group comparison of the PIPP-R scores will be performed using an ANCOVA, where the covariate will be the GA stratification variable. If the overall comparison is significant at the 5% level, then the paired comparisons will be performed using a similar ANCOVA model. An appropriate multiple comparison Bonferroni procedure will be used to control the overall type I error probability. To conduct the subgroup analysis for GA, an interaction term will be added to the ANCOVA model. In each trial the binary adverse events variables will be compared using a multiple logistic model with intervention group and GA as independent variables. To control for multiplicity due to the number safety variables, a 5% significance will be used.

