### Outcomes {12}

#### Noxious-related brain activity

Noxious-related brain activity will be measured from a pain-related event-related potential [14–16, 41] induced by a clinically required heel lance measured using a dense-array neonatal EEG recording. The primary outcome attributed to the clinically required heel lance will be a noxious-related N420-P560 event-related potential (ERP) which will specifically be examined and isolated at electrode Cz as previous research has reported pain-related activity at this site in both neonates [14, 16, 42] and adults [43].

The EEG data will be recorded using a 32 channel HydroCel Geodesic Sensor Net connected to a GES 400 EEG system (EGI, Eugene, OR, USA). Electrodes will be submerged for 5 min in a solution of warm water and infant shampoo. Electrode impendences will be checked to ensure they are below the impedance threshold of 100 kΩ. NetStation Acquisition software (version 5.2.0.2) will be used for recording of EEG activity from 0.5 to 30 Hz with a sampling rate of 1000 samples per second and a conversion of 24 bit. For all infants, regardless of randomization, data collection will begin with a continuous recording of a one-minute baseline of all outcome measures while the infant is resting in their incubator or cot (BL1). Following this, a non-noxious (NN1) control stimulus will be applied to the infant’s foot to capture a baseline response on EEG to a non-painful event. This non-noxious (sham) stimulus will consist of placing the heel lance against the foot and rotating it 90 degrees, so that when the lance is released it mimics the sensation of the heel lance procedure without the associated tissue-breaking and pain. The infant will then be placed in their assigned intervention group and will be re-exposed to the non-noxious control stimulus, followed by the clinical heel lance.

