### Sample size {14}

Using a priori data [15], we will require 63 participants per group (total sample size of 126 for the two groups) to detect a 30% reduction in amplitude of the pain-specific ERP on EEG during the clinically required heel lance. The sample size calculation accounts for multiple testing across intervention groups and is based on a type I error probability of 5% and power of 80% [54]. Sixty-three participants per group also allows us to detect the smallest clinically important difference of one on the PIPP-R scale, with a standard deviation of two, considered a clinically relevant difference between the active interventions of SSC and 24% oral sucrose [55].

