### Plans to promote participant retention and complete follow-up {18b}

Follow-up is completed within minutes of finishing the procedure; therefore, it is unlikely there will be missing data due to loss to follow-up.

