### Data management {19}

Collection of both bio-behavioural data and pain-specific ERPs on EEG have been previously demonstrated in clinical trials with this patient population [16, 57]. A challenge that may be encountered during data collection is loss of physiologic data (e.g. heart rate and electrophysiologic measurements) due to equipment failure or movement artefact. EEG procedures will be employed to control for and limit loss due to artefact. Research personnel experienced in EEG techniques will be present during data collection to monitor data recordings and make prompt adjustments in the instance of any recording malfunctions to limit data loss.

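### The PIPP-R ANCOVA is valid but adjusts only for the GA stratum; prespecifying the pre-treatment (BL1) behavioural measure as a second covariate would be a cheap efficiency gain of uncertain size

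*Protocol article*

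**What the plan says.** The Pain intensity paragraph of Statistical methods {20a} fixes the model: "An overall between-group comparison of the PIPP-R scores will be performed using an ANCOVA, where the covariate will be the GA stratification variable". It names no second covariate. Because the covariate is stated, this is a choice the article makes and not a detail left open for an analysis plan.

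Under Outcomes {12}, Noxious-related brain activity, the sequence is the same for all infants whatever their allocation: "data collection will begin with a continuous recording of a one-minute baseline of all outcome measures while the infant is resting". This is BL1. A non-noxious sham stimulus (NN1) follows, and only then is the infant placed in the assigned intervention. The sham is repeated on treatment before the heel lance.

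The Pain intensity paragraph under Outcomes {12} says that PIPP-R variables are scored as changes from baseline, that GA is one of the seven variables, and that the three facial actions will also be analysed separately.

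Sample size {14} sizes this outcome: "Sixty-three participants per group also allows us to detect the smallest clinically important difference of one on the PIPP-R scale", with an SD of two.

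**The concern.** A pre-treatment behavioural measurement is taken in every infant, yet the PIPP-R model does not use it as a covariate. The covariate that is named belongs in the model because randomisation was stratified on GA. But GA is itself a scored PIPP-R item, and the stratum says nothing about how active the individual infant's face was before treatment.

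What is at stake is precision on a secondary outcome whose sizing has no slack. The article allows for no losses: it expects that "it is unlikely there will be missing data due to loss to follow-up". Data management {19} nevertheless foresees "loss of physiologic data (e.g. heart rate and electrophysiologic measurements) due to equipment failure or movement artefact", and heart rate and saturation are PIPP-R components. A prognostic baseline covariate is one of the few ways to gain some margin without recruiting more infants.

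**Working it through.** **Inputs from the article (Sample size {14}).** Difference 1 and SD 2 on PIPP-R, 63 per group, type I error 5%, power 80%. The last two are stated for the ERP calculation in the same paragraph and are taken to apply here as well. Sidedness is not stated; two-sided is assumed.

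**Input not in the article.** The partial correlation r between the BL1 measure and the heel-lance PIPP-R, given the GA stratum. It is assumed over a range. SD 2 is taken as the SD within GA stratum.

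**Step 1: reproduce the stated size.** The normal approximation is n = 2·SD²·(z₀.₉₇₅ + z₀.₈₀)²/difference² = 2·4·(1.960 + 0.842)²/1 = 62.79, rounded up to 63. Power at 63 is 80.1% by this approximation. With the noncentral t, the noncentrality is 1/(2·√(2/63)) = 2.81 on 124 df, which gives 79.5%; 64 per group would be needed to pass 80%. The stated figure is confirmed, and it has no margin.

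**Step 2: add a covariate.** The residual SD becomes 2·√(1 − r²). The model has an intercept, group, GA stratum and covariate, which leaves 126 − 4 = 122 df. With 63 per group:

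| r | residual SD | power (t) | n per group for 80% (normal) |
|---|---|---|---|
| 0 | 2.00 | 79.5% | 63 |
| 0.1 | 1.99 | 79.9% | 63 |
| 0.2 | 1.96 | 81.1% | 61 |
| 0.3 | 1.91 | 83.1% | 58 |
| 0.4 | 1.83 | 85.9% | 53 |
| 0.5 | 1.73 | 89.5% | 48 |

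The first row is the downside. If the covariate carries no information, power is unchanged at 79.5% despite the lost degrees of freedom. Only r² matters, so a negative correlation (an infant already active at baseline has less room to rise) helps as much as a positive one.

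**Step 3: with some losses.** Assume 10% unusable records, for illustration, which leaves 56 per group. Power (t) is 74.6% without the covariate, 78.5% at r = 0.3 and 81.6% at r = 0.4. The covariate offsets such a loss only if r is about 0.4 or more.

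**The case against.** The strongest reply is that nothing here is wrong. ANCOVA on the stratification factor keeps the type I error, chance imbalance between arms is already reflected in the standard error, and 63 per group reproduces. All of that stands, and it is why the point is only a recommendation.

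A second reply is that baseline information is already in the outcome, because the article describes every PIPP-R variable, facial items included, as change from baseline. This also stands and makes a low r plausible. It does not remove the point: a baseline-referenced score can still be adjusted for its pre-treatment baseline without bias, and doing so uses whatever association remains.

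A reader might go further and infer that each infant's untreated pain response was recorded and then ignored. The documents do not support that. No infant is lanced without intervention (Trial design {8}). NN1 is a painless sham whose stated purpose is an EEG baseline, and it is not among the four marked phases for physiological and behavioural data. No PIPP-R score at NN1 is promised. The facial video is described for the painful procedure (Who will be blinded {17a}), so footage at NN1 cannot be assumed. What the article does state for all infants is BL1, and the recommendation is confined to that.

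Finally, the table's gains need the partial correlation given GA. A marginal correlation, part of which may run through GA, could overstate them.

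**Conclusion.** The point holds as a minor, optional improvement. The article names only the GA stratum for PIPP-R while recording a pre-treatment baseline of all outcome measures in every infant. The planned analysis is neither biased nor invalid, and the sample size is not in error; a reader should not take the 79.5% as showing an undersized trial, since it differs from 80.1% only through the t distribution.

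The gain is under 2 power points for r up to 0.2, about 3.6 points at r = 0.3 (79.5% to 83.1%) and 10 points at r = 0.5 (79.5% to 89.5%). This rests on an assumed r, on SD 2 holding within GA stratum, on a two-sided 5% test and on complete data. The covariate is not a substitute for an allowance for lost records. The primary ERP analysis is not affected.

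**What to change.** In the Pain intensity paragraph of Statistical methods {20a}, state before allocation is revealed to the analysts that the PIPP-R and facial-action ANCOVAs adjust for the GA stratum and for the infant's BL1 facial-action score.

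- Define the scoring window. BL1 lasts one minute under Outcomes {12}, but Plans for assessment {18a} gives two minutes.
- Use a response to the pre-treatment sham (NN1) only if it was recorded and scored for all infants.
- Do not use the on-treatment sham as a covariate, because the intervention can affect it.
- Keep infants with a missing BL1 score in the analysis under a prespecified rule, for example a single imputed value that ignores allocation, so that the covariate does not cost sample size.

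The cost is a sentence or two of wording, one degree of freedom, and a short extra segment for up to 126 infants, scored by the existing blinded coders with the existing software. If BL1 video was not kept for most infants, leave the model as planned.

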#### Adverse events

Mean frequency of occurrence of each of the safety surveillance outcomes will be compared across the groups using *t*-tests, with post hoc tests for intervention condition as appropriate.

### Interim analyses {21b}

One analysis of the primary outcome is planned at study end. There are no plans for an interim analysis.

### Methods for additional analyses (e.g. subgroup analyses) {20b}

A subgroup analysis based on GA will be conducted.

### Methods in analysis to handle protocol non-adherence and any statistical methods to handle missing data {20c}

It is not anticipated that there will be an issue with protocol non-adherence given that data are collected over a single intervention and that participants are infants.

### Plans to give access to the full protocol, participant level-data, and statistical code {31c}

The protocol will be freely available through an open access publication. There are no plans to have participant-level dataset, and statistical code readily available, however, individual requests will be considered.

## Oversight and monitoring

### Composition of the coordinating centre and trial steering committee {5d}

The PI will be responsible for the overall program of research. A 0.5 FTE Research Coordinator will be hired for the day-to-day management of the trial including study personnel, under the supervision of the PI.

The PI, Co-I’s, and Research Coordinator will comprise the RCT Steering Committee. The Steering Committee will meet bi-monthly in year one, quarterly thereafter in person and via teleconference, and at the end of the study to discuss results and dissemination.

### Composition of the data monitoring committee, its role and reporting structure {21a}

A data safety monitoring committee (DSMC) will be established consisting of three individuals (with expertise in neonatology, neuroscience, or biostatistics), independent of the investigators who have no financial, scientific, or other conflicts of interest with the trial.

### Adverse event reporting and harms {22}

The collection, assessment, and reporting of adverse events and other unintended effects of trial interventions or trial conduct will be done in accordance with Good Clinical Guideline Practices and Research Ethics Board (REB) approvals.

### Frequency and plans for auditing trial conduct {23}

All study documents will be kept in accordance with Good Clinical Guideline Practices and REB approvals. There are no planned audits, however, institutional auditing of clinical trials independent from investigators occur routinely.

### Plans for communicating important protocol amendments to relevant parties (e.g. trial participants, ethical committees) {25}

If any important protocol modifications (e.g. changes to eligibility criteria, outcomes, analyses) are required, communication of these changes will made through online portals (i.e. ethics, ClincialTrials.gov.), or email reports will be forwarded to relevant parties (e.g. investigators, REB, trial participants, trial registries, journals, regulators).

### Dissemination plans {31a}

Knowledge translation initiatives will be ongoing throughout the research process, with initial emphasis on raising healthcare professional and public awareness and interest in newborn pain management followed by increased knowledge and changing behaviours through updating of relevant policies and practices. Regular updates on the progress of the study will be provided to health professionals and managers on the participating unit via face-to-face meetings. When results from the study become available, focus will also be placed on targeting researchers, healthcare providers, administrators, and decision makers with new knowledge to inform newborn pain assessment and management practices, as well as subsequent research in the field. Three reports (1, 3, and 10 pages) will be generated for key clinical and policy stakeholders to disseminate the findings of the study. These reports will be disseminated nationally and internationally through existing affiliations with the Canadian Neonatal Network, Canadian Association of Pediatric Health Centres, Canadian Pediatric Society, both Canadian and International councils of Neonatal Nurses, Vermont Oxford Neonatal Network, and Nordic Pain in Early Life Association. Traditional end of grant knowledge translation initiatives targeting researchers and knowledge users will include publication in high impact academic peer-reviewed journals (e.g. Pediatrics, JAMA Pediatrics, PAIN, Birth), presentation at national and international conferences (e.g. International Symposium on Pediatric Pain, Canadian Pain Society Annual Scientific Meeting, Pediatric Academic Society, Council of International Neonatal Nurses), and presentations and webinars to key clinical decision makers and healthcare providers in the clinical setting locally and worldwide (e.g. Family Centered Care Council, National Canadian Premature Baby Association and March of Dimes). Our team has a strong online presence and will share study results as appropriate over social media platforms including Facebook and Twitter, as well as press releases to raise widespread public, healthcare provider, and parent awareness. Collectively, our team has contributed to practice change in our local institutions and worldwide through clinical practice guidelines. The PI and several members of the team regularly give public presentations (e.g. CIHR Café Scientifique) and disseminate research findings through print, radio, and television media. A YouTube video produced by the PI for parents to reduce pain in newborns has been viewed > 165,000 times in > 152 countries and was awarded first place in the inaugural CIHR Video Talks Competition. Moreover, the Centre for Pediatric Pain Research (CPPR), where the PI is based, has successfully reached millions of parents and care providers through the CIHR funded “It Doesn’t Have to Hurt” initiative in partnership with YummyMummyClub.ca to improve pain care for children.

## Discussion

To the best of our knowledge, we will be the first sufficiently powered randomized clinical trial examining the effect of SSC provided during a medically indicated heel lance on pain induced activity in the preterm brain compared to the provision of 24% sucrose.

### Why might maternal-infant skin-to-skin contact (SSC) be different?

Tactile perception is one of the first senses of fetal development, emerging at approximately seven to eight weeks gestation [62]. Thus, all newborns have the ability to perceive physical touch and demonstrate positive responses to stroking or massage [63]. Human infants have been shown to demonstrate reduced behavioural stress and improved sleep following gentle human touch [64, 65] and massage [66, 67]. Additionally, animal models of neonatal touch have demonstrated increases in endorphins, oxytocin, and serotonin—hormones that have been associated with modulating pain response [68–71]. While no studies to date have examined the neural mechanisms underlying the analgesic effect of touch on pain responses in infants, there is evidence to suggest that simple touch modulates nociceptive specific responses in adults [72]. When A delta and C nociceptors were selectively activated by high power laser pulses in healthy adults, application of tactile stimulation significantly reduced cortical laser-evoked potentials [72] and laser blink reflex (which is generated by brain stem circuits before nociceptive signals reach the cortex) [72]. This suggests a blunting of both cortical and sub-cortical nociceptive responses secondary to tactile stimulation.

Evidence related to SSC demonstrates significant benefit such as stabilization of physiologic parameters (e.g. temperature, heart, and respiratory rates), decreased occurrence of apneas, improved weight gain and growth, and accelerated maturation of autonomic and circadian systems [63, 73–77]. Related to this proposal, SSC has demonstrated benefit as an effective pain-relieving intervention for infants undergoing needle-related procedural pain [78]. In a recent update of our Cochrane systematic review and meta-analysis, including 25 studies (*n* = 2001 infants), SSC significantly reduced composite pain scores measured by the PIPP [46] at 30 (*n* = 268, MD − 3.21, 95% CI − 3.94 to − 2.48), 60 (*n* = 164, MD − 1.85, 95% CI − 3.03 to − 0.68), and 90 (*n* = 163, MD − 1.34, 95% CI − 2.56 to − 0.13) s following painful procedures. Of note, while holding a clothed baby provides some comfort, it appears that direct SSC is significantly more effective [79]. The underlying mechanisms of SSC are thought to be associated with blunting of sympathetic nervous system responses and up-regulation of parasympathetic nervous system responses through physiological neural regulators [80]. Specifically, SSC may elicit an inborn tactile receptor response that regulates vagal tone and release of endogenous opiates, oxytocin, and beta-endorphins [81, 82]. This proposed mechanism of action differs significantly from the primary gustatory mechanism of sweet tasting solutions. As such, it is highly plausible that SSC may inhibit nociceptive responses in the preterm brain [60, 83].

### Summary and justification for the proposed research

While there is strong evidence of the effectiveness of oral sucrose and SSC to reduce bio-behavioural responses to pain, based on the current standard of assessment, optimal pain management in the NICU is precluded by our lack of understanding of the effect of these interventions on (a) noxious pain-related responses in the neonatal brain, (b) the efficacy of SSC when compared to sucrose on noxious pain-related brain activity, and (c) the relationship between noxious-evoked brain activity and bio-behavioural responses to noxious stimuli in preterm infants. The proposed research study will address these significant gaps. The results of the study may help increase awareness and inform behaviour change and practice regarding the importance of parent presence and engagement in pain care in the NICU.

## Trial status

The trial is currently in the recruitment phase. Recruitment began on November 19, 2018 and is estimated to be completed on September 30, 2022. Protocol Version 1.0 (23OCT2018).

## Data Availability

The Principal Investigator and study team will have access to the final trial dataset.

## Abbreviations

ANOVA: Analysis of variance
ANCOVA: Analysis of covariance
BS: Behavioural state
CPPR: Centre for Pediatric Pain Research
DSMC: Data Safety Monitoring Committee
EEG: Electroencephalography
ERP: Event-related potential
fMRI: Functional magnetic resonance imaging
GA: Gestational age
iCAP mini: The influence of skin-to-skin contact on Cortical Activity during Painful procedures in preterm infants in the neonatal intensive care unit
mN: Millinewtons
NTISS: Neonatal Therapeutic Interventions Scoring System
NICU: Neonatal intensive care unit
NIRS: Near-infrared spectroscopy
PAiN: Pain Assessment in Neonates
PCA: Principal Component Analysis
PCs: Principal components
PI: Principal Investigator
PIPP: Premature Infant Pain Profile
PIPP-R: Premature Infant Pain Profile Revised
REB: Research Ethics Board
SNAP II: Score for Neonatal Acute Physiology-II
SSC: Skin-to-skin contact
